**Methods:**

We will conduct a stepped-wedge cluster randomized controlled trial study of 869 adult patients with hypertension attending two NCD clinics to test the effectiveness, acceptability, and fidelity of a CHW-led intervention. The multi-component intervention will be centered on monthly household visits by trained CHWs for a period of 1 year, consisting of the following: (1) blood pressure and sugar monitoring, (2) BMI monitoring, (3) cardiovascular disease risk assessment, (4) using checklists to guide monitoring and referral to clinics, and (5) healthy lifestyle counseling and education. During home visits, CHWs will remind patients of follow-up visits. We will measure blood pressure at baseline and 3-monthly for the entire cohort. We will conduct individual-level mixed effects analyses of study data, adjusting for time and clustering by patient and community.

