### Study design

The study will employ a closed cohort, superiority stepped wedge cluster randomized design. There will be a sequential crossover of clusters from the control to the intervention arms and the order of the cross over will be randomly determined (Fig. 1). This study will be conducted in 21 clusters within Nakaseke district. Each cluster will consist of 4–5 villages (Table 1). Participant recruitment will occur before randomization. At the beginning of the study period, we will collect baseline demographic data from each of the participants. All the villages within the study will eventually receive the intervention, thereby improving equity and acceptability. To minimize contamination, we will ensure that clusters are well separated to minimize social contact between participants in the intervention and control arms. Since all clusters will be observed under both the intervention and control arm, we anticipate that imbalances are less likely to occur. To further address the issue of contamination, individuals within the same cluster will be randomized to receive the intervention at the same time. Also, since the study will be conducted in a rural population, we expect adjacent neighborhoods to be far apart from each other, and this could additionally reduce the rates of contamination within the study area. In addition, CHW activities are directed to individuals at the level of the home and not large community groups or gatherings. This should decrease exposure of non-enrolled patients from outside randomized clusters to the interventions. We plan to rollout the intervention in two clusters per month and one cluster in the final month (Fig. 2).

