### Sample size determination

The primary outcome will be a change in systolic blood pressure between the intervention and control group. To compute the required sample size for the step wedge design, we first computed the required sample size if we were to implement an individual randomized trial. By conservative estimates, we estimate a 6-mmHg difference in systolic blood pressure between the intervention and control group [20, 21]. Accounting for the stepped-wedge design and constant cluster sizes (40) within the sample, with a fixed number of clusters (*n* = 21) and a power of 90%, at 0.05% level of significance, a sample size of 869 will power the study to detect an absolute minimally important clinical difference (MCID) of 6 mmHg in the mean systolic blood pressure between the intervention and control arms. We intend to roll out the intervention within two clusters each month and within one cluster during the final month.

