### Data analysis

Patient characteristics will be summarized using proportions for categorical variables. Means (standard deviations) and medians (interquartile ranges) will be used for continuous variables by exposure period (intervention and control periods). The chi-square and Fisher’s exact test will be used to test for differences in participant characteristics for categorical variables by exposure period status. The one-way ANOVA will be used to compare means between the two periods for normally distributed continuous variables, and Kruskal-Wallis test will be used for non-normally distributed continuous variables.

We will follow the intention-to-treat principle, and clusters will be analyzed according to their randomized crossover time irrespective of whether crossover was achieved at the desired time. Mixed effects logistic regression models will be used to assess the impact of the intervention on the primary outcome. These models will be fitted with time treated as a fixed effect at each step. Also, since calendar time is hypothesized to be associated with both the exposure (intervention) to the intervention and the outcome, we will adjust for this as a potential confounder in the final analysis. To account for dependence between individual measurements, an additional random effect for individuals in the study will be added into the model. The estimated intra-cluster correlation and time effect from the fitted model will be reported for use in the design of future trials and to allow appreciation of any underlying confounding effects of calendar time. The period a particular cluster has been exposed to the intervention will be accounted for in the final model as an effect modifier. For the secondary binary outcomes, we intend to employ the same methods as above for analysis. However, linear mixed-effects models accounting for temporal trends will be used to assess the intervention impact on the different continuous secondary outcomes. In the case of missing data, we will capitalize on multiple imputation techniques to handle the issue of missing data in this study.

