## Discussion

We discuss the rationale, methods, and protocols for the CHW-HTC closed cohort stepped wedge cluster randomized trial in Uganda. The overall goal of the trial is to evaluate the effectiveness of a CHW-led intervention in blood pressure control among confirmed hypertensive patients in a rural Ugandan community. Based on our statistical power calculations, we will work with a fixed number of 21 clusters, enrolling 40 participants in each cluster. Similar studies have proven applicability across various settings, strengthening our theory-informed approach. A number of studies show that CHWs can be effective in delivering patient management strategies. A randomized controlled trial based in Nepal proves that a female community health worker intervention could effectively reduce mean systolic blood pressure in hypertensive patients [26]. A Mexican-based study indicates that a CHW-led intervention among hypertensive or diabetic patients is associated with a twofold increase in the odds of disease control [27]. Similarly, a CHW-led intervention in the USA to improve hypertension management among Filipino Americans with uncontrolled blood pressure finds that blood pressure was controlled at a significantly greater percentage among the treatment group participants (83.3%) compared to the control group (42.7 %) [21].

We will follow 11 phases of implementing the intervention, introducing it within two clusters at each step of the trial and within one cluster in the final step (Fig. 2). Clusters will be assigned randomly to intervention rollout while one CHW will be attached to each cluster. We will center our intervention on monthly pro-active household visits by trained CHWs over a study period of 1 year. A local non-government organization and a multinational research group with wide-ranging experience in conducting research in rural communities will carry out the study. The local coordination will support overcoming economic and cultural barriers to enrollment and support the establishment of community trust. This clinical trial builds upon previous research and collaborations in LMIC settings investigating the advantages of engaging CHWs in the patient-centered management of hypertension.

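### The random effects named (community and patient) hold the within-cluster correlation constant over time; if it decays, the standard error of the intervention effect is too small

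*Protocol article*

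**What the plan says.** The Abstract (Methods) sets out the analysis in one sentence: "We will conduct individual-level mixed effects analyses of study data, adjusting for time and clustering by patient and community". The Data analysis section treats time as a fixed effect at each step and continues: "To account for dependence between individual measurements, an additional random effect for individuals in the study will be added into the model". The word for an added effect implies that a cluster effect is already in the model. The same section promises the intra-cluster correlation, in the singular, for the design of later trials. It also brings in length of exposure as an effect modifier, which is a fixed term.

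Neither place mentions a cluster-by-time random effect, a correlation that decays with time, a robust variance or a small-sample correction.

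On the design: "This study will be conducted in 21 clusters within Nakaseke district", with "constant cluster sizes (40) within the sample" and a total of 869. It is a closed cohort, measured at baseline and every 3 months, with two clusters crossing over per month and one in the last of eleven phases.

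**The concern.** A cluster intercept and a patient intercept, with time effects common to all clusters, imply that a cluster sits at a fixed distance above or below the common trend for the whole study. Any community-specific movement between rounds is then counted as independent noise in single patients and averaged away over the cluster.

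In a closed-cohort stepped wedge, the intervention effect is estimated largely from change within clusters over time. Cluster-by-time fluctuation enters exactly there, and averaging over more patients in the same cluster does not reduce it. If such fluctuation exists and the model has no term for it, the confidence interval for the primary effect is too narrow and the false-positive rate exceeds the nominal level. A single reported ICC would also mislead the later trials it is meant to serve, since a stepped-wedge design needs the between-period correlation as well.

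**Working it through.** **The plan's own figure.** The article states no type I error for its model. Its only related figure is the sample size ("a sample size of 869 will power the study to detect" 6 mmHg), and it cannot be reproduced because neither the SD nor the ICC is given. 21 × 40 = 840, not 869; 869/21 = 41.4, so 41 per cluster is used below.

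**Inputs from the article.** 21 clusters; 41 patients each; ten monthly steps of two clusters and one step of one; measurements at 0, 3, 6, 9 and 12 months.

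**Assumed inputs.** Linear model for systolic pressure; constant effect; no dropout; two-sided 5% test (the article prints "a power of 90%, at 0.05% level of significance"); SD 20 mmHg, which cancels out of the error rate; ICC 0.01 to 0.05; cluster autocorrelation (CAC) 0.8 to 1; individual autocorrelation (IAC) 0.5 to 0.7.

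**Variance components.** With total variance σ² and m patients per cluster:
- permanent cluster effect = σ² × ICC × CAC
- cluster-by-occasion effect = σ² × ICC × (1 − CAC)
- patient effect = σ² × (1 − ICC) × IAC
- residual = σ² × (1 − ICC) × (1 − IAC)

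**One case by hand (ICC 0.05, CAC 0.8, IAC 0.5).** σ² = 400. The components are 16, 4, 190 and 190. The occasion-specific variance of a cluster mean is:
- in truth: 4 + 190/41 = 8.63
- in the model without the term: (4 + 190)/41 = 4.73

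The approximate ratio of model SE to true SE is √(4.73/8.63) = 0.74.

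**Full calculation.** Generalised least squares on cluster-occasion means, with the working covariance (cluster and patient only) set against the true covariance in a sandwich variance, gives a model SE of 0.782 and a true SE of 1.051 mmHg, ratio 0.744. Type I error = 2Φ(−1.96 × 0.744) = 14.5%. The other cases, each for IAC 0.5 to 0.7:

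| ICC | CAC | Model SE / true SE | Type I error |
|---|---|---|---|
| 0.01 | 0.9 | 0.96 to 0.94 | 5.9 to 6.5% |
| 0.02 | 0.8 | 0.87 to 0.81 | 8.7 to 11.2% |
| 0.05 | 0.9 | 0.84 to 0.77 | 9.9 to 13.1% |
| 0.05 | 0.8 | 0.74 to 0.65 | 14.5 to 20.0% |
| 0.05 | 1 (no decay) | 1.00 | 5.0% |

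A 24-month schedule gives nearly the same error rates.

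**Simulation.** REML fits to 600 to 800 null trials per scenario (Monte Carlo error about 1 point, IAC 0.6, z test) gave, without the term: 5.2% with no decay, 5.8% at 0.01/0.9, 9 to 10% at 0.02/0.8, 11 to 12.5% at 0.05/0.9 and 17% at 0.05/0.8. Under first-order autoregressive decay at 0.8 per 3 months and ICC 0.05 it reached 25%. With a cluster-by-occasion intercept, the same scenarios gave 5 to 7.5% (z) and about 3 to 5% (t, 19 df).

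**The case against.** The strongest reply is that the article never lists its random effects as complete. It names levels of clustering and one added effect. As a condensed article it may leave a further variance term and the degrees-of-freedom method to a fuller document. A reader might infer that the plan rules out a cluster-by-occasion term; it does not say so. What remains is that the levels it does state, with common time effects and one ICC, describe a constant-correlation model, and nothing in the text points to another.

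A reader might also infer that the standard error is too small as a matter of fact, or that some particular inflated rate applies. The documents do not support that. The inflation needs decay, and the article gives no ICC or autocorrelation from which to judge it.

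Nor is the number of clusters the cause. Both standard errors shrink together as clusters are added, and with the right structure 21 clusters give about 5 to 7.5% on a z test. The cause is the omitted term combined with about 41 patients per cluster.

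The sources of fluctuation that come to mind are only partly convincing. All patients attend two clinics, so a clinic-wide shock is at least partly absorbed by the common time effects. It is true that "one CHW will be attached to each cluster", but that worker delivers the intervention while research assistants take the study measurements, so differences between workers are mainly differences in effect. Decay is therefore plausible but not documented.

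Finally, the figures are for a linear, constant-effect model, whereas the Data analysis section names logistic regression for the primary outcome. Because that outcome is mean systolic pressure, the linear model is the natural basis for the check, but the conflict is a separate point.

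**Conclusion.** The point holds conditionally. The random structure named forces a constant within-cluster correlation over time. If the correlation decays between rounds, the test of the primary effect is anti-conservative: about 6% at ICC 0.01 with cluster autocorrelation 0.9, about 9 to 13% in the middle of the range examined, and up to 20% at ICC 0.05 with autocorrelation 0.8. Steady autoregressive decay can take it higher. Without decay there is no inflation. All these figures rest on assumed correlations, a linear model, equal clusters and no dropout; none can be derived from the article. The remedy is cheap and protects the primary result, so it should be made before the analysis is fixed.

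**What to change.** In the primary model for mean systolic pressure, specify fixed occasion effects and random intercepts for cluster, cluster-by-occasion and individual. Fit by REML with a small-sample degrees-of-freedom correction (Kenward–Roger, for example). Report the within-period and the between-period ICC in place of one ICC. Resolve the logistic model named for the continuous primary outcome in the same revision.

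The cost is one variance component and a somewhat wider interval. In the hand-worked case the half-width goes from 1.96 × 0.782 = 1.5 mmHg to about 1.96 × 1.051 = 2.1 mmHg. If there is no decay, the extra variance is estimated near zero and little is lost, although the t reference with 19 df was then slightly conservative in simulation (about 3%). Against the planned effect ("we estimate a 6-mmHg difference in systolic blood pressure between the intervention and control group"), 6/1.051 = 5.7 standard errors, so under these assumptions and a constant effect, power is not at risk.

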### Primary outcome

Decrease in the average systolic pressure between the intervention and control arms.

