### Intervention

The multi-component intervention will be centered on monthly pro-active household visits by trained CHWs for a period of 1 year.

It will consist of the following:Blood pressure and sugar monitoring. CHWs will be trained in measuring blood pressure using a digital blood pressure machineBMI monitoringCardiovascular disease risk assessmentUse of checklists to guide monitoring and referral to the clinics. Checklists will be filled in and handed over to the project staff for review at the end of every weekHealthy lifestyle counseling and education. CHWs will be trained in a curriculum regarding home health education and strategies regarding behavioral change communication. The education will be provided to participants and all the family members during the home visitFollow-up during home visits to ensure that patients received all prescribed medications and to encourage them to adhere to themProviding patient-education using PocketDoktor™ booklets, an established education tool among hypertensive patients in rural settings [22]

During home visits, CHWs will remind patients of follow-up visits and encourage clinic attendance.

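### A single patient random intercept assumes equal correlation at every time gap; if correlation decays, standard errors can be too small, by an amount set by the decay and the length of follow-up

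*Protocol article*

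**What the plan says.** The article describes a closed cohort: "We will measure blood pressure at baseline and 3-monthly for the entire cohort". The abstract promises mixed-effects analyses "adjusting for time and clustering by patient and community". The Data analysis section gives the structure: "These models will be fitted with time treated as a fixed effect at each step", and, for dependence between readings, "an additional random effect for individuals in the study will be added into the model". It mentions no serial correlation and no robust variance. It also plans to treat a cluster's length of exposure as an effect modifier.

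Two other statements bear on the point.

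- **Model type.** The section says "Mixed effects logistic regression models will be used to assess the impact of the intervention on the primary outcome", while the primary outcome is "Decrease in the average systolic pressure between the intervention and control arms", a continuous quantity. Linear models are named only further on: "linear mixed-effects models accounting for temporal trends will be used to assess the intervention impact on the different continuous secondary outcomes".
- **Length of follow-up.** The Intervention section describes "monthly pro-active household visits by trained CHWs for a period of 1 year", and rollout takes 11 monthly phases. If each cluster receives a year of visits, readings run to about 11 + 12 = 23 months. The Discussion, however, gives one year for the study period, and Data monitoring places an interim look at 12 months with clusters still to cross over.

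**The concern.** With one intercept per patient and independent residuals, any two readings on a patient have the same correlation. Blood pressure readings close in time are usually more alike than readings far apart. In a stepped wedge each cluster switches once and stays switched, so slow drift in patients' pressures can look like a step change. A model that ignores the drift can then report too small a standard error, or weight the readings inefficiently.

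The patient level is not negligible here. With an assumed SD of 20 mmHg and ICC of 0.02, the variance of a cluster's mean at one round has a cluster part of 400 × 0.02 = 8.0 mmHg² and a patient part of 400 × 0.98 / 40 = 9.8 mmHg².

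**Working it through.** **Plan's own figure.** The article states no standard error, SD, ICC or within-patient correlation, so there is nothing to reproduce on this point. Its sample size of 869 cannot be rebuilt either; 21 × 40 = 840 is used below.

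**Inputs from the article.** 21 clusters of 40; two clusters crossing per month and one in the last (months 1–11); readings every 3 months; fixed time effects; cluster and patient intercepts.

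**Assumed inputs.** SD 20, ICC 0.02, two-sided 5%, a linear model, and one of these within-patient correlations at a gap of g months:

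- A: 0.35 + 0.50 × 0.6^(g/3), the rest visit noise (0.65, 0.53, 0.41, 0.36 at 3, 6, 12, 24 months)
- B: 0.7^(g/3) (0.70, 0.49, 0.24, 0.06)
- C: 0.7 × 0.9^(g/3), slow decay with visit noise (0.63 at 3 months, 0.46 at 12)
- D: 0.6 at every gap, no decay

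**Formulas.** For a cluster's vector of round means, the true covariance is V = 8.0·J + 9.8·R, where J is all ones and R is the pattern above. The stated model uses M = a·J + (b·J + e·I)/40, with a, b and e at the values REML tends to under the true pattern. X is the design matrix of one cluster.

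- Model SE: from (ΣX′M⁻¹X)⁻¹
- True SE: from (ΣX′M⁻¹X)⁻¹ (ΣX′M⁻¹VM⁻¹X) (ΣX′M⁻¹X)⁻¹
- Best SE: from (ΣX′V⁻¹X)⁻¹
- Test size: 2Φ(−1.96 × model SE / true SE)

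**Constant effect, model / true / best SE in mmHg:**

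| Pattern | Readings to 12 months | Readings to 24 months | Model/true at 24 | Test size at 24 |
|---|---|---|---|---|
| A | 0.749 / 0.736 / 0.707 | 0.723 / 0.803 / 0.697 | 0.90 | 7.8% |
| B | 0.775 / 0.743 / 0.652 | 0.796 / 0.933 / 0.651 | 0.85 | 9.5% |
| C | 0.735 / 0.716 / 0.705 | 0.711 / 0.771 / 0.688 | 0.92 | 7.1% |
| D | 0.710 / 0.710 / 0.710 | 0.639 / 0.639 / 0.639 | 1.00 | 5.0% |

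At 12 months model/true is 1.00–1.04, so the test is about right or slightly conservative. The precision loss is 0.736/0.707 = 1.04 (A), 0.743/0.652 = 1.14 (B), 0.716/0.705 = 1.02 (C) and none (D).

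Pure autoregressive decay with a 3-month correlation of 0.5 to 0.9 gives model/true of 0.885 down to 0.83 at 24 months, that is 11.5–17% too small. At 12 months the loss in SE under that decay is 8–14% for 3-month correlations of 0.5–0.7, and reaches 20% only at 0.9.

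The ratio does not depend on SD and hardly on ICC: from ICC 0.005 to 0.10 it stays at 0.90 (A) and 0.85 (B).

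**With a linear exposure-duration term (form assumed), model/true:**

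| Pattern | At crossover, 12 months | After 6 months' exposure, 12 months | At crossover, 24 months | After 6 months' exposure, 24 months |
|---|---|---|---|---|
| A | 1.02 | 1.239/1.404 = 0.88 | 0.98 | 0.95 |
| B | 1.05 | 1.276/1.559 = 0.82 | 0.98 | 0.92 |

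**Simulation.** Patient-level data with REML fits, constant effect, nine rounds, 350 runs per setting (Monte Carlo error about 1.2–1.6 points). The stated model had size 8.9% (A) and 9.7% (B). Adding an autoregressive residual gave 6.6% and 6.3%, and the empirical SE fell from 0.802 to 0.709 and from 0.929 to 0.659. With a cluster-by-round effect both true and fitted, size without the decaying residual was still 9.4% in both patterns.

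**Power.** For the constant effect the true SE is at most about 1 mmHg, so 6/1 − 1.96 = 4.04 and power exceeds 99.9%. For the six-month effect under B at 12 months, 6/1.559 − 1.96 = 1.89, about 97%.

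**The case against.** The strongest objection is that residual covariance, variance estimator and small-sample correction are details that a condensed article may leave to an analysis plan, and that the article does not rule out serial correlation. This stands in part: silence on a robust variance is no finding in itself. But the article does choose a dependence structure, and the point concerns what that choice implies.

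A reader might infer stronger claims that the documents do not support:

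- **That the standard error is 10–15% too small as a fact.** That size needs fairly strong decay. Slow decay gives less and no decay gives zero, and the article gives nothing to choose between them.
- **That follow-up is 24 months.** It is only inferred, and the statements on study length conflict.
- **That over 12 months only precision is at stake.** This holds for a constant effect, but not once exposure duration is in the model, as the article intends.
- **That the percentages apply to the primary model as named.** That model is logistic, and the figures do not carry over to a log odds ratio. The mismatch between a logistic model and a continuous outcome is the more basic error.

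It is also fair that the decaying residual alone did not bring size fully to 5% in simulation. Part of the excess may come from having only 21 clusters, which is why the fix includes a small-sample correction.

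**Conclusion.** The point holds in conditional form. The stated random intercept implies no decay in within-patient correlation. If there is decay, the standard error of a constant effect is roughly right over 12 months of readings, with a loss from negligible to about 14% in SE for 3-month correlations up to about 0.7. Over about 24 months it is 0–17% too small, a test size of about 5–10%. With a linear exposure-duration term, the standard error of the effect after some months of exposure can be about 5–18% too small under decay even at 12 months.

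These figures rest on the assumed correlation patterns, the form of the duration term and a linear model. The ability to detect 6 mmHg is not in doubt at the assumed SD. What is affected is type I error, interval coverage and efficiency. The change is cheap and worth making.

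**What to change.** First name a linear mixed model for systolic pressure, and reconcile the statements on study length in Intervention, Data monitoring and Discussion so that the last round of readings is fixed.

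Then, for systolic pressure and the other continuous outcomes:

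1. Keep the cluster and patient random effects, and add a within-patient residual correlation that decays with the months between readings (first-order autoregressive or exponential).
2. Base tests and intervals on a small-sample correction for 21 clusters.
3. If that model does not converge, use the stated structure with a cluster-robust, small-sample-corrected standard error.
4. Report the estimated decay alongside the intra-cluster correlation already promised.

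The cost is a few sentences in the analysis section, one extra covariance parameter, slightly slower fitting and a small risk of non-convergence, which the fallback covers. No new patients, visits or data are needed. If correlation hardly decays, little is lost.
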